### Study participants

The study will include all nurses working in primary healthcare units, such as family health units, primary healthcare centres, among others, who express interest in the programme, agree to participate in the study, regardless of professional category or experience or academic qualifications. Participants who give informed consent but fail to attend all six sessions will be excluded from the study.

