**Method:**

The intervention group will participate in the PPAPEP, consisting of six training sessions, each lasting 3 hours. The programme’s goal is to empower nurses by providing knowledge about what constitutes a positive nursing practice environment and equipping them with tools to improve their practice environment. The outcomes of the intervention will be assessed both at the end of the programme and 3 months after its conclusion.

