### Sample size

Considering the study’s objective, we calculated the sample size using G*Power software (version 3.1.9.6) with a two-tailed test to compare two dependent means (Student’s *t*-test). The parameters used included an effect size of 0.5, a significance level (α) of 0.05, and a statistical power (1-β) of 0.80. The calculation suggests a minimum total sample size of 34 participants (17 participants per group). The allocation ratio between the groups will be 1:1. Thus, we aim to recruit at least 34 nurses working in primary healthcare units who are interested in and agree to participate in the study.

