### Outcomes evaluation

Participants will complete a sociodemographic questionnaire, and the programme’s effectiveness will be assessed using two instruments: the shortened version of the Scale for the Environments Evaluation of Professional Nursing Practice (SEE-Nursing Practice)^
39
^ and Safety Attitudes Questionnaire (SAQ) — Short Form.^
40
^

The SEE-Nursing Practice consists of 59 items across three subscales: structure (29 items); process (19 items); and outcome (11 items). Participants rate each item on a five-point Likert scale (1: never to 5: always). Higher scores indicate a more favourable NPE for care quality and professional wellbeing. Scores are interpreted as follows:<35% (unfavourable), 35–55% (moderately favourable), 55–75% (favourable), and>75% (very favourable).^
39
^

The SAQ — Short Form 2006 assesses healthcare professionals' perceptions of patient safety attitudes. It has been previously validated and culturally adapted to the context in which the study will be conducted.^
40
^ The SAQ — Short Form 2006 comprises six dimensions, addressing organisational factors, work environment factors, and team factors, with a total of 30 items. Participants respond to each item using a five-point Likert scale ('strongly disagree' to 'strongly agree'). The final score ranges from 0–100, where 0 represents the worst perception and 100 the best perception of the safety climate.^
40
^ The timing of the outcome measures and data collection evaluation moments are detailed in Table 2, following SPIRIT guidelines and the extension for reporting trial protocol outcomes.^
36
^

**Table 2. table2:** Outcome measures and data collection evaluation moments

Activity	Study period					
	T – 1 (Pre-allocation)	EM0 (baseline)	EM1 (pre-intervention)	Intervention period	EM2 (post-intervention)	EM3 (follow-up)
Enrollment						
- Participants' information	X					
- Participants express interest in PPAPEP	X					
- Participant consent	X					
- Random group allocation		X				
Intervention: PPAPEP			—	—	—	—
Outcomes						
Data collection:						
- Demographic and professional data	X					
- Scale for the Environment's Evaluation of Professional Nursing Practice — Shortened Version		X	X		X	X
- Safety Attitudes Questionnaire — Short Form		X	X		X	X
- Qualitative data from participants’ knowledge during intervention				X		

EM = evaluation moment. PPAPEP = Positive Nursing Practice Environments Promotion Programme

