### Strengths and limitations

Results from this study will be reported in accordance with CONSORT guidelines and disseminated through peer-reviewed scientific journals and conferences focused on this field. Despite efforts to minimise bias, it is possible that nurses expressing interest in this training programme already have prior awareness of the topic, potentially influencing their perceptions of the NPE and patient safety (this may represent some level of performance bias). Some participants may be unable to attend all sessions owing to professional or personal reasons; to prevent this bias (dropout bias), sessions will be offered on two different days and at varied times. This study marks a significant advancement in the exploration of NPE, not only by analysing the outcomes of a training intervention for primary healthcare nurses, but also through its rigorous study design.

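### Excluding nurses who miss any of the six sessions is a post-randomisation exclusion that turns the trial into a completers-only comparison, and the protocol does not say which arms it covers

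*Protocol article*

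**What the plan says.** Under Study participants the protocol article sets this rule: "Participants who give informed consent but fail to attend all six sessions will be excluded from the study". The programme is described in the abstract as "consisting of six training sessions, each lasting 3 hours". In Table 2 (Outcomes evaluation) the row "Random group allocation" is marked at EM0, ahead of the intervention period.

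Under Control intervention, control nurses also take the programme later, but only their EM0 and EM1 questionnaires, both completed before their own sessions, are used. Under Strengths and limitations the authors expect missed sessions: "Some participants may be unable to attend all sessions owing to professional or personal reasons". They call this dropout bias and respond with a choice of days and times. Data analysis promises a flowchart of exclusions and dropouts, and a Student's t-test between groups. It does not say that randomised nurses are analysed as allocated whatever their attendance.

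The sample size is a "minimum total sample size of 34 participants (17 participants per group"), and the recruitment target is set at that figure with no allowance for exclusions.

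**The concern.** Attendance at six sessions can be known only after allocation. Removing nurses on that basis means the groups compared are no longer the groups that were randomised. The wording removes them from the study itself, not merely from a per-protocol set, so their later questionnaires may never be collected.

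The filter may not be neutral. Both primary outcomes are nurses' perceptions of their practice environment and safety climate, and missed sessions are attributed partly to professional reasons. A link between attendance and outcome is therefore plausible, though the article gives no evidence of its strength or sign.

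The scope of the rule is also open. If it applies only to the intervention arm, a selected group is compared with an unselected one. If it applies to both, control nurses are discarded for events that come after their last used outcome, EM1. Neither is the comparison that randomisation supports, and both reduce a small sample.

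**Working it through.** **The plan's own figure.** Inputs from Sample size: "two-tailed test to compare two dependent means" and "an effect size of 0.5, a significance level (α) of 0.05, and a statistical power (1-β) of 0.80". For a paired t-test, power comes from the noncentral t distribution with n − 1 degrees of freedom and noncentrality d√n. With d = 0.5 and two-sided α = 0.05, n = 33 gives 0.795 and n = 34 gives 0.808. The stated 34 is reproduced, as 34 pairs.

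**How strict an all-six rule is.** The article gives no attendance rate. Assume per-session attendance p, independent between sessions; the share attending all six is p⁶.

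| Assumed p | p⁶ | Full attenders of 17 (17 × p⁶) | Excluded |
|---|---|---|---|
| 97% | 0.833 | 14.2 | 16.7% |
| 95% | 0.735 | 12.5 | 26.5% |
| 90% | 0.531 | 9.0 | 46.9% |

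Independence is the harsh case. With an assumed within-person correlation of 0.3, 95% attendance leaves about 84% complete and 90% leaves about 71%.

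**Reading A: only the intervention arm is filtered.** Let ρ be the correlation between attendance propensity and outcome, q the share excluded and z the normal quantile at q. With no programme effect, the mean of the remaining nurses shifts by ρφ(z)/(1 − q) SD. With an assumed ρ = 0.3:

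- q = 0.167: 0.3 × 0.2502/0.833 = 0.09 SD (18% of the planned 0.5 SD)
- q = 0.265: 0.3 × 0.3275/0.735 = 0.13 SD (27%)
- q = 0.469: 0.3 × 0.3977/0.531 = 0.22 SD (45%)

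Simulated type I error of the between-group t-test is about 6–8% in the last two cases, against a nominal 5%. A negative ρ would reverse the shift.

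**Reading B: both arms are filtered, by the same mechanism.** The same model gives a mean difference of about 0 SD and type I error of about 5%. The bias in the between-group difference disappears; the restriction to full attenders and the loss of sample remain.

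**Power of the between-group t-test at d = 0.5.** Noncentral t with n₁ + n₂ − 2 degrees of freedom and noncentrality d√(n₁n₂/(n₁ + n₂)). Starting from 17 v 17: 0.5 × √(289/34) = 1.46, power 29%.

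| | Intervention arm only filtered | Both arms filtered |
|---|---|---|
| p = 95% | 12 v 17: 25% | 12 v 12: 22% |
| p = 90% | 9 v 17: 21% | 9 v 9: 17% |

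**On the plan's own paired formula.** Assumed losses of 10%, 20% or 30% leave 15, 13 or 11 per arm, that is 30, 26 or 22 in total. Power falls from 0.81 to 0.75, 0.69 or 0.61.

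**The case against.** A reader might infer that the rule pushes the intervention-arm mean upward, because nurses in overloaded units attend least. The document does not support this. The rule speaks of participants and names no arm. Controls take the same programme later. Under Allocation, randomisation, and blinding, allocation is said to be unknown to researcher and participants until data collection ends, so exclusions made along the way could not be made by arm. The reading closest to the text is that both arms are filtered, and then the shift is about zero if attendance works alike in both. No passage says which nurses miss sessions; the sign and the 0.3 correlation are assumptions. This objection stands, and it limits the bias figures to reading A.

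Several further points stand in part:

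- Most of the low between-group power comes from splitting a paired-test sample into 17 per arm. At the two lower assumed attendance rates the rule takes a further 4 to 8 points if one arm is filtered and 7 to 12 if both are. The 34 is a minimum, so higher enrolment would ease this.
- Flexible scheduling lowers the number of missed sessions, and the flowchart will show the exclusions. Neither makes the removal of the remaining nurses neutral. Selecting questionnaires blind to allocation does not undo selection by attendance.
- The rule could be read as removing only nurses who attend no session. The limitations text favours missing any, and either way the exclusion follows randomisation.
- A separate analysis plan may define analysis sets, but it would have to override a rule that the protocol states outright.
- Recruitment took place in September and October 2024, and questionnaires are anonymous and self-coded, so the change needs more than a new sentence.

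**Conclusion.** The concern holds in this form. The protocol fixes an adherence-based exclusion after randomisation, so following it as written gives a comparison of full attenders, not of all randomised nurses. That needs no assumption beyond the rule and the timing of allocation in Table 2.

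The size is conditional. If both arms are filtered and attendance mechanisms are equal, there is little bias in the between-group difference, and the costs are a narrower target population and the larger power loss (29% to about 22% or 17%). Control nurses attend later, so equality of mechanism is not guaranteed. If only the intervention arm is filtered, the spurious shift is about 0.09 to 0.22 SD under the assumed 0.3 correlation and independent attendance of 97% to 90%, in a direction that the document does not establish. Because the rule affects both primary outcomes and can be replaced at modest cost, it should be changed.

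**What to change.** Delete the exclusion sentence under Study participants. State instead that:

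- every randomised nurse stays in the study and is asked for all scheduled questionnaires whatever the attendance, with a route for nurses who stop attending to return EM2 and EM3 under their own code;
- the primary analysis compares all randomised nurses as allocated;
- the number of sessions attended is reported;
- the six-of-six analysis is kept as a labelled sensitivity analysis that states which arms it filters.

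If data collection is already complete, apply the as-allocated analysis to every nurse whose questionnaires are held, and report how many were lost through the exclusion.

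Keeping everyone needs no larger sample than the plan already states. The cost is an amendment to the eligibility and analysis text, a little follow-up effort within the anonymous coding system, and slight dilution of the estimate by partial attenders.

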### Participant selection, recruitment, and consent

Participants will be recruited through the institution’s training centre. The training centre coordinator will send all nurses employed at the institution information about the programme, along with a link to the informed consent form, a registration form, and a declaration of interest in participating. Each participant’s declaration of interest will be coded using an algorithm provided by the research team, ensuring data anonymisation and preventing the investigator from identifying participant allocation. Study design and workflow is presented in Figure 1.

**Figure 1. fig1:**
[figure not shown]
Study design and workflow. PPAPEP = Positive Nursing Practice Environments Promotion Programme

### Participant retention strategies

To minimise dropouts and improve participant retention, a schedule with the dates and times of each session will be sent to all participants, allowing them to choose their preferred session day and time in advance.

### Sample size

Considering the study’s objective, we calculated the sample size using G*Power software (version 3.1.9.6) with a two-tailed test to compare two dependent means (Student’s *t*-test). The parameters used included an effect size of 0.5, a significance level (α) of 0.05, and a statistical power (1-β) of 0.80. The calculation suggests a minimum total sample size of 34 participants (17 participants per group). The allocation ratio between the groups will be 1:1. Thus, we aim to recruit at least 34 nurses working in primary healthcare units who are interested in and agree to participate in the study.

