## How this fits in

Positive nursing environments play a crucial role in enhancing care quality, safety, and professional wellbeing. The Positive Nursing Practice Environments Promotion Programme (PPAPEP) is a validated programme to improve nursing practice environments. Conducting a clinical trial to assess the effectiveness of PPAPEP is essential to understand its impact on the safety climate and practice environments. The results of this study may provide definitive and reliable evidence for strategies and future nursing practice improvements, and may support the development of institutional policies to improve nursing care.

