### Data analysis

Following the CONSORT guidelines,^
37
^ a flowchart outlining participants’ progression throughout the study will be created. This will include information on sample size, reasons for exclusions, and participant dropouts.

Data analysis will be performed by the research team, with preliminary steps including verification of data discrepancies, potential biases, anomalies, incomplete or missing data, as well as assessments of distribution normality, linearity, and homoscedasticity. These steps ensure compliance with prerequisites for subsequent statistical analyses.

Demographic and professional characteristics of participants will be analysed using descriptive statistics. This will involve measures of central tendency, variance metrics, frequency charts, and 95% confidence intervals for all subgroups.

The analysis will include group comparison tests appropriate for the type of variable under study. A univariate analysis will assess each variable before and after the intervention. Bivariate analyses will examine correlations between dependent and independent variables, while multivariate analyses will explore interactions and relationships among them.

Primary outcomes will focus on participants’ perceptions of the NPE and safety climate in primary healthcare settings. The Student’s *t*-test will be used to compare group mean values, and the paired *t*-test will examine changes within groups. Effect size interpretations will use Cohen’s D index, categorised as small (0.2–0.49), moderate (0.5–0.8), or large (>0.8).^
41
^

Multivariate analysis will include linear regression for dependent variables such as nurses' perceptions of the practice environment and safety climate in primary health care. If assumptions of normality, homoscedasticity, and variable independence are not met, variable transformation will be considered. After regression analysis, the adequacy of the model in representing the observed data will be evaluated, along with the possibility of changes in variable effects.^
42
^

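### The 34-nurse sample size is a count of pairs for a single-group paired t-test, halved into two arms of 17; the stated 80% power falls to about 29% between groups and 49% within a group

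*Protocol article*

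**What the plan says.** The Sample size section of the protocol article bases the calculation on a Student's t-test, "with a two-tailed test to compare two dependent means", with "an effect size of 0.5, a significance level (α) of 0.05, and a statistical power (1-β) of 0.80". It reports the result as "The calculation suggests a minimum total sample size of 34 participants (17 participants per group") and adds: "The allocation ratio between the groups will be 1:1". The Abstract repeats 34 as the minimum.

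Under Study design and settings the trial is randomised, controlled and parallel. Under Data analysis, the primary outcomes (practice environment and safety climate) get two kinds of test: Student's t-test "will be used to compare group mean values, and the paired" t-test for changes within groups. Under Control intervention, only the control group's assessments from before it receives the programme count. The box How this fits in says that the results "may provide definitive and reliable evidence".

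**The concern.** A calculation for two dependent means returns a number of pairs, here people in one group who each give a before and an after value. It does not return a total to be shared between randomised arms. If 34 is such a count, splitting it 17 and 17 leaves every planned test with fewer observations than the calculation requires, and the quoted 80% power describes none of them.

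The randomised comparison is what would show that the programme works. A reader who trusts the 80% would take a non-significant difference as fair evidence against a moderate effect. At the real power, a true effect of the assumed size would more often than not give a non-significant result.

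**Working it through.** **Inputs (Sample size section).** Two-sided test, alpha 0.05, target power 0.80, standardised effect 0.5, 34 in total, 17 per group, 1:1. The article gives no SD, no correlation between repeated measurements and no dropout allowance. All figures use the exact noncentral t distribution.

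**Step 1: reproduce the stated figure.** For a paired t-test with n pairs, df = n − 1 and the noncentrality is dz × √n, where dz is the mean difference divided by the SD of the differences.

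- n = 33: 0.5 × √33 = 2.872, power 79.5%.
- n = 34: 0.5 × √34 = 2.915, power 80.8%.

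So 34 is the smallest number of pairs that reaches 80%.

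**Step 2: see whether another calculation gives 34 as a two-arm total.** A one-sided paired test needs 27 pairs. A two-sample t-test needs 64 per arm two-sided or 51 per arm one-sided. None gives 34 in total. The 34 is the paired count from Step 1.

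**Step 3: power of the planned tests at 17 per arm.**

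| Planned test | df | Noncentrality | Power |
|---|---|---|---|
| Between groups, d = 0.5, 17 v 17 | 2 × 17 − 2 = 32 | 0.5 × √(17/2) = 1.458 | 29.3% |
| Within one group, dz = 0.5, 17 pairs | 17 − 1 = 16 | 0.5 × √17 = 2.062 | 49.1% |

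**Step 4: what the between-group test needs, and what 17 per arm can detect.**

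- Size for d = 0.5: 63 per arm gives 79.5% and 64 per arm gives 80.1%, so 64 per arm, 128 in total.
- Effect detectable at 80% power with 17 per arm: d = 0.99 between groups, dz = 0.72 within a group.
- Half-width of the 95% confidence interval for the unadjusted group difference: 2.037 × √(2/17) = 0.70 SD, wider than the 0.5 assumed.

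**Step 5: could baseline adjustment recover the power?** This needs a baseline-to-outcome correlation r, which the article does not give, so these values are assumptions. If 0.5 is in SDs of the raw score, adjustment divides the effect by √(1 − r²).

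| Assumed r | Power, 17 per arm | Detectable effect, 0.991 × √(1 − r²) |
|---|---|---|
| 0.5 | 37% | 0.86 SD |
| 0.7 | 51% | 0.71 SD |
| 0.8 | 65% | 0.59 SD |

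Power reaches 80% only at r of about 0.86. The Data analysis section mentions linear regression but names no baseline covariate.

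**The case against.** The strongest objection is that 0.5 is used on two scales. In a dependent-means calculation it is dz, in SDs of the within-person difference. The 29% uses it as a between-group d. The two agree for change scores, and for post-programme scores when r = 0.5. If dz = 0.5 is carried over to a comparison of post-programme scores, d = 0.5 × √(2(1 − r)), and power at 17 per arm is 39% at r = 0.3, 29% at r = 0.5, 19% at r = 0.7 and 15% at r = 0.8. On the same reading, baseline-adjusted power is about 37% at r = 0.5 and 34% at r = 0.7; it does not rise to 51%. This stands as a point of labelling: each figure must carry its scale. It does not bring the planned between-group test near 80%.

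Second, 34 is a minimum, and the number enrolled is not shown. That is fair, but at d = 0.5 power is only 34% with 20 per arm and 48% with 30 per arm.

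Third, control nurses eventually take the programme, so all 34 might supply before-and-after pairs. The Control intervention section rules this out, because it uses only their assessments from before the programme.

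Fourth, the phrase about definitive evidence is hedged and sits in a summary box, and presenting results as estimates with intervals is a choice of style. Both are fair: these are consequences of the error and not part of the arithmetic.

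**Conclusion.** The concern holds. The arithmetic behind 34 is right for one group measured twice, but the split into two arms is wrong, and the stated 80% power belongs to no test in the plan. At the stated minimum, power is about 29% for the between-group t-test and about 49% for each within-group paired test.

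The 29% takes 0.5 as the between-group standardised difference with no baseline adjustment; the 49% takes 0.5 as dz. Both assume that all 17 nurses per arm are analysed. The Study participants section excludes nurses who do not attend all six sessions, and the calculation states no allowance for this, so real power could be lower. Baseline adjustment would help only to the extent of a correlation that the article does not give.

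**What to change.** Rewrite the sample-size paragraph for the between-group comparison:

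- Say that 34 is the number of pairs for a single-group paired test, and delete the claim that 34 in total gives 80% power for an effect of 0.5.
- State that with 17 per arm the unadjusted between-group t-test has about 29% power for d = 0.5 and can detect about 1.0 SD with 80% power. Give the within-group figure too: about 49% with 17 pairs at dz = 0.5.
- If a baseline-adjusted analysis is adopted, name it in Data analysis. Quote its power (about 37% to 51%) and detectable effect (about 0.9 to 0.7 SD) only with the assumptions stated: r from 0.5 to 0.7, and the effect in SDs of the raw score.
- Restate these figures for the number actually enrolled, since recruitment is reported as having taken place.

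It would also be sensible to report the group differences as estimates with 95% confidence intervals and to drop the word definitive from How this fits in.

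The cost is a few sentences and a less favourable stated power. No further enrolment is asked for.
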